### Sample size

The sample size was calculated according to the changes in anandamide level, in response to weight loss, based on the study conducted by Mallipedhi et al. [16]. It was calculated considering 95% confidence interval, 80% power (α = 0.05 and β = 0.2), and the related mean and SD of anandamide levels in the mentioned study (μ1 = 0.297; μ2 = 0.209; SD1 = 0.042; SD2 = 0.049). Finally, 30 subjects were recruited for each group.

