### Randomization

Eligible subjects will be stratified according to age and BMI randomly assigned to one of two groups: **control** (standard weight loss group, *n* = 30) and **intervention** (whey supplementation weight loss group, *n* = 30).

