### Intervention

All participants will follow a hypocaloric diet of 800 kcal below estimated energy requirements, energy needs is estimated by Mifflin Jeor St equation. Control group will follow a hypocaloric diet of 800 kcal below estimated energy requirements and intervention group will follow a hypocaloric diet of 916 kcal below estimated energy requirements, each of intervention group subjects will receive 30-g whey protein powders daily. The powders will be provided in a sachet form (each sachet containing 30-g whey protein). Each 30 g of the whey protein supplement will be contained 116 kcal, 0.5 g of lipid, 0.4 g of carbohydrate, and 27.5 g of protein. Participants will be instructed to add one sachet to 250 ml cold water and consume immediately, every evening. In control and intervention group the macronutrients percent will be carbohydrate 55%, fat 30% and protein15%. Subjects will be asked to record powder intake and to check compliance, they will be followed by the dietitian via phone calls or SMS, every three days and, powders will be given to the subjects every 15 days. To create a variety in the diet while maintaining the general principles of diet, the same dietitian will give a dietary exchange list and a diet according to their food habits. A trained dietitian will design the energy requirements and macronutrient distribution and the same dietitian will be available to train participants on the diet.

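### The sample-size inputs give 5 to 6 women per arm, not 30, and they describe a response to weight loss rather than the whey-versus-control difference, so the stated 80% power does not apply to the randomised contrast

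*Protocol article*

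**What the plan says.** The Sample size section of the protocol article gives the basis as follows: "The sample size was calculated according to the changes in anandamide level, in response to weight loss", with figures taken from an earlier published study. The design inputs are "95% confidence interval, 80% power (α = 0.05 and β = 0.2"), the means "μ1 = 0.297; μ2 = 0.209" and the standard deviations "SD1 = 0.042; SD2 = 0.049". The section closes with "Finally, 30 subjects were recruited for each group". It states no dropout allowance, multiplicity adjustment or other reason for the number 30.

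The Intervention section says "All participants will follow a hypocaloric diet of 800 kcal below estimated energy requirements". It then sets the food plan at 800 kcal below requirements in the control arm and 916 kcal below in the whey arm, where each daily sachet supplies 116 kcal. Only the intervention arm receives whey ("whey supplementation weight loss group, *n* = 30", Randomization section). The section on aims and hypotheses makes the effect of whey in women on a weight-loss diet the primary question. The Analysis section plans t-tests between and within groups, and ANCOVA adjusted for baseline.

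**The concern.** Two things do not fit. First, a difference of 0.088 against SDs below 0.05 is very large (almost two SDs), and such a difference needs only a handful of women per arm. Second, the difference describes what weight loss does to anandamide, whereas the randomised comparison is between two groups that are both dieting.

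This is the only sample-size justification in the article. A reader who sees 80% power may take a null between-arm result as reasonable evidence that whey has no effect on anandamide. The statement does not support that reading, because the 80% was attached to a different effect.

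**Working it through.** **Inputs** (all from the Sample size section): alpha 0.05, taken as two-sided because a 95% confidence interval is mentioned; power 80%; means 0.297 and 0.209; SDs 0.042 and 0.049; allocation 1:1 (Randomization section).

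**Step 1: try to reproduce 30 per arm.**

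- Difference: 0.297 − 0.209 = 0.088.
- Sum of variances: 0.042² + 0.049² = 0.004165. Pooled SD: √(0.004165/2) = 0.0456. Standardised difference: 0.088/0.0456 = 1.93.
- n per arm = (1.960 + 0.842)² × (SD1² + SD2²)/difference² = 7.849 × 0.004165/0.007744 = 4.22, so 5.
- Exact t-test power: 76% at 5 per arm, 85% at 6, over 99.9% at 30.

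The stated 30 is not reproduced. Variants do not rescue it:

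| Variant | n per arm |
|---|---|
| One-sided 0.05 | 4 |
| Two-sided, 90% / 95% / 99% power | 6 / 7 / 10 |
| Larger SD (0.049), 99% power | 12 |
| Paired design, baseline-end correlation 0 or above | at most 5 subjects |
| Change scores, correlation 0 (SD 0.0645) | 9 |
| The two SDs added together in error (0.091) | 17 |

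Reaching 30 needs an SD of about 0.12, more than twice either stated value, or dropout of 1 − 6/30 = 80%.

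**Step 2: compare the effect sized with the effect tested.**

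- Effect sized: the anandamide response to weight loss, 0.088.
- Effect tested: whey against no whey, in women who are all on a restricted diet. The implied net deficit is 916 − 116 = 800 kcal in the whey arm and 800 kcal in the control arm. The article does not print this net figure, but it follows from the stated energy values.

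The response to energy restriction is therefore expected largely in both arms, and the between-arm difference is what whey adds. The article states no expected value for that difference.

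**Step 3: what 30 per arm can detect.** The pooled SD of 0.0456 is carried over as an assumption. Figures are for a two-sided t-test at 0.05.

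| Assumed share of 0.088 added by whey | Between-arm difference | Unadjusted power, 30 per arm |
|---|---|---|
| 50% | 0.044 | 96% |
| 40% | 0.0352 | 84% |
| 30% | 0.0264 | 60% |
| 25% | 0.022 | 45% |
| 10% | 0.0088 | 11% |

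Difference detectable with 80% power:

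- 30 per arm, unadjusted: 0.736 SD, or 0.736 × 0.0456 = 0.034, which is 38% of 0.088.
- 30 per arm, ANCOVA with an assumed baseline-end correlation of 0.5: 0.736 × √(1 − 0.5²) = 0.637 SD, or 0.029.
- 24 per arm analysed (assumed), unadjusted: 0.826 SD, or 0.038, which is 43% of 0.088.

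**The case against.** The strongest reply is that the article never says the formula yielded 30. The closing sentence can be read as a deliberate choice above a computed minimum, and an article may leave out an inflation step. Against the stated inputs, the discrepancy is also on the safe side. Part of this stands: 30 may well have been chosen for other reasons. But the section presents 30 as the end of the calculation, ordinary dropout cannot take 6 to 30, and the mismatch of contrasts remains either way.

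A reader might infer three stronger things that the document does not support:

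- *That the trial is underpowered.* The article gives no whey effect on anandamide and says in its Background that this effect is unclear. No share of 0.088 can be called realistic. Power is good at 40% or more and poor at 25% or less, and the planned baseline adjustment helps: at a 25% share it raises power from 45% to 56% if the correlation is 0.5.
- *That the design does not estimate the weight-loss response at all.* It does, through the within-group paired tests. The narrower statement is correct: 0.088 is not the between-arm contrast.
- *That the weight-loss effect cancels exactly.* The Background offers greater fat loss as a reason for higher protein intake, so the two arms need not respond identically. The response is expected to be largely, not wholly, common to both.

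A further caution stands. The source study is not at hand, and an SD near 0.12 would give 30, so a misprinted SD cannot be excluded. The detectable differences above would then change too.

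**Conclusion.** The point holds in two parts. The printed inputs lead to 5 to 6 women per arm, and no standard variant comes near 30. Separately, 0.088 is a weight-loss response that both arms should largely share, so the 80% power claim does not carry over to whey versus control.

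The first part is arithmetic on the article's own figures. The second rests on the article's description of the source figure and on the equal implied net deficit. The size of the consequence depends on assumptions the article cannot settle: the SD of 0.0456, the share of the effect that whey adds, the baseline-end correlation and the number of women analysed. Whether 60 women are enough is therefore open. What is established is that the stated justification does not answer that question.

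**What to change.** Keep 60 women and rewrite the paragraph:

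1. Check the two SDs and means against the source study and correct them if they are misprinted.
2. Remove the implication that 30 follows from 0.297 versus 0.209, or state the actual reason for choosing 30.
3. State the sensitivity for the randomised contrast. Possible wording, if the SDs are confirmed: *With 30 women per arm, the trial has 80% power (two-sided 0.05) to detect a between-arm difference in end-of-trial anandamide of about 0.034 (0.74 SD) without adjustment, about 0.029 with baseline-adjusted ANCOVA, and about 0.038 without adjustment if 24 per arm are analysed. These figures assume an SD of 0.0456 and, for ANCOVA, a baseline-end correlation of 0.5; the number of 24 is also an assumption.*
4. Add a sentence on whether a difference of that size would be worth detecting, since a detectable difference derived from n does not justify itself.

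The cost is one paragraph of wording and a less favourable stated sensitivity. It needs no extra participants and no change to the analysis.

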### Randomization

Eligible subjects will be stratified according to age and BMI randomly assigned to one of two groups: **control** (standard weight loss group, *n* = 30) and **intervention** (whey supplementation weight loss group, *n* = 30).

### Intervention

All participants will follow a hypocaloric diet of 800 kcal below estimated energy requirements, energy needs is estimated by Mifflin Jeor St equation. Control group will follow a hypocaloric diet of 800 kcal below estimated energy requirements and intervention group will follow a hypocaloric diet of 916 kcal below estimated energy requirements, each of intervention group subjects will receive 30-g whey protein powders daily. The powders will be provided in a sachet form (each sachet containing 30-g whey protein). Each 30 g of the whey protein supplement will be contained 116 kcal, 0.5 g of lipid, 0.4 g of carbohydrate, and 27.5 g of protein. Participants will be instructed to add one sachet to 250 ml cold water and consume immediately, every evening. In control and intervention group the macronutrients percent will be carbohydrate 55%, fat 30% and protein15%. Subjects will be asked to record powder intake and to check compliance, they will be followed by the dietitian via phone calls or SMS, every three days and, powders will be given to the subjects every 15 days. To create a variety in the diet while maintaining the general principles of diet, the same dietitian will give a dietary exchange list and a diet according to their food habits. A trained dietitian will design the energy requirements and macronutrient distribution and the same dietitian will be available to train participants on the diet.

### Measurements

A questionnaire about patients’ demographic situations, diseases, and medications, diabetes history and probable supplementations will be recorded at the beginning of the study. Dietary intake will be assessed by 3 days 24-h recall questionnaires (2 week days and 1 weekend day) at the baseline, middle and the end of study. Total energy and macronutrients intake will be calculated by using Nut IV (the Hearst Corporation, San Bruno, CA). To assess physical activity levels the International Physical Activity Questionnaire (IPAQ) will be used at the baseline and the end of study. Anthropometric parameters will be measured after overnight fasting with minimal clothing and without shoes. In all visits (every 15 days), body weight will be measured with the accuracy of 100 g using seca scale. Stature will be measured in a relaxed position using seca stadiometer with accuracy of 0.5 cm. BMI will be calculated as body weight (kg) divided by the square of height(m). Waist circumference will be assessed at above the iliac crest, just below the lowest rib margin at the end normal expiration to the nearest 0.5 cm. TANITA BC-418 body composition analyzer will be used to calculate total body fat and fat percent, fat free mass and fat free mass percent.

At baseline and end of the trial, 10 ml of venous blood samples (2 ml in EDTA- coated sterile tubes and 8 ml in regular tubes) will be collected after 10–12 h overnight fasting. For determination of plasma AEA and 2-AG, the blood in EDTA coated tubes will be centrifuged at 1500 g at 4 °C for 15 min and will be stored at -80 °C. These variables will be quantified by liquid chromatography/in-line mass spectrometry [7]. Regular tubes will be used for biochemical analyses such as determination of glucose, insulin, total cholesterol, HDL-C, triglyceride, adiponectin, leptin, TNF-α and IL-6 in serum. Blood glucose and lipid profile will be determined by enzymatic method with kits from Pars-azmoon (Tehran, Iran). LDL-C levels will be calculated by the Friedewald equation. Circulating insulin will be measured by immunoassay. Homeostasis model assessment – insulin resistance(HOMA-IR) will be calculated by the following formula: fasting glucose(mg/dl) × fasting insulin(μu/ml)/405. ELISA kits will be used to measure serum adiponectin and leptin levels.

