### Participants

Subjects will be 60 premenopausal obese women aged 18 years or more. The following inclusion criteria will be applied: aged 18 years and older, BMI range of 30 to 40 kg/m^2^, absence of menopause, lactation, pregnancy and food allergies, not having cancer, hepatic, renal, thyroid and gastrointestinal disorders, no surgery for weight loss, no weight loss over the past 6 months, no taking herbs and drug that reduce appetite and weight and vitamin-mineral supplements. The participants with any of the following criteria will be excluded: become pregnant during study, unwilling to continue. At the end of the intervention, if the remained powders exceed 10% of total administered powders, that subject will be excluded from the study.

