### Analysis

SPSS version 17 (SPSS Inc., Chicago, IL, USA) will be used for data analysis. All data will be presented as mean ± SD. The percent change of each variable will be also calculated by the formula [(E − B)/B × 100], where E is the end of treatment values and B is the baseline values. The normality of variables will be tested using Kolmogorov- Smirnov test. Independent sample t-test and the paired sample t-test will be applied for comparing parametric continuous data between and within the groups, respectively. Mann-Whitney test and Wilcoxon test will be used to test the differences in asymmetric variables between and within the groups, respectively. To control confounding variables, analysis of covariance (ANCOVA) test were used to determine the differences between the two groups post-intervention, while adjusting for baseline measurements and covariates. A *p* value less than 0.05 will be considered to be statistically significant.

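### Weight is recorded every 15 days but the stated analyses use only baseline and end values, so women who stop early add nothing to the 2-month weight and BMI comparison

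*Protocol article*

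**What the plan says.** Measurements sets the weighing schedule: "In all visits (every 15 days), body weight will be measured with the accuracy of 100 g using seca scale". BMI is derived from weight and height, so it too is available at each visit. The 15-day schedule is stated for weight only. Blood is drawn at baseline and at the end.

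Analysis then lists the methods:
- Percent change is defined for each variable by a formula "where E is the end of treatment values and B is the baseline values".
- For the simple tests: "Independent sample t-test and the paired sample t-test will be applied for comparing parametric continuous data between and within the groups, respectively", with Mann-Whitney and Wilcoxon as the alternatives for asymmetric variables.
- ANCOVA is used "to determine the differences between the two groups post-intervention, while adjusting for baseline measurements and covariates".

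Participants adds two exclusion rules: "The participants with any of the following criteria will be excluded: become pregnant during study, unwilling to continue", and, at the end of the intervention, "if the remained powders exceed 10% of total administered powders, that subject will be excluded from the study".

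No stated analysis uses the weights taken between baseline and end.

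**The concern.** Each stated analysis is a two-time-point analysis. Combined with the rule that removes women unwilling to continue, it gives a completers-only comparison for weight and BMI.

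Two things are at stake. The first is precision: with 30 women per arm, each one lost matters, and her interim weights would recover part of what she loses. The second is bias. The trial is open label, both arms are on an energy-restricted diet, and only one arm has a daily powder to take. Stopping could plausibly be related to how much weight a woman has lost so far, or differ between arms. Baseline adjustment does little about this, because baseline weight says little about the loss achieved by day 30. The interim weights do carry that information.

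**Working it through.** **Plan's own figure.** There is none to reproduce. The protocol states no drop-out rate and no power or sample size for weight or BMI; its 30 per group is derived from anandamide.

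**Step 1. Follow one woman through the plan.** Taking 2 months as 60 days, weights fall at about days 0, 15, 30, 45 and 60. Suppose she stops after the day-30 visit.

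| Stated analysis | Needs | Can she enter? |
|---|---|---|
| Percent change, (E − B)/B × 100 | B and E | No, E is missing |
| Paired t / Wilcoxon | both values | No |
| Independent t / Mann-Whitney on end value or change | end value | No |
| ANCOVA of the post-intervention value | end value | No, outcome missing |
| Exclusion of women unwilling to continue | – | Removed in any case |

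Her weights at days 0, 15 and 30 exist but have no stated use. The powder rule works differently: it applies at the end, when an end weight may exist, so it removes data rather than responding to missing data.

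**Step 2. Precision lost if such women contribute nothing.** With n completers per arm, the standard error of an end-value comparison is SD × √(2/n), so relative to 30 it rises by √(30/n). The difference detectable with 80% power at two-sided 5% is (1.960 + 0.842) × √(2/n) SD. The drop-out rates are assumptions.

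| Drop-out | n per arm | √(30/n) | Detectable difference (SD) |
|---|---|---|---|
| 0% | 30 | 1.00 | 0.72 |
| 10% | 27 | 1.05 | 0.76 |
| 20% | 24 | 1.12 | 0.81 |
| 30% | 21 | 1.20 | 0.86 |

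**Step 3. What the interim weights recover.** This is an illustrative simulation with 3,000 trials per setting and 30 per arm. Everything else is assumed: a true difference of −1.0 kg at day 60, SDs of weight change rising from 1.0 kg at day 15 to 2.5 kg at day 60, and correlation 0.85 between adjacent visits. Completers-only is the difference in mean day-60 change. The alternative fills missing later weights by sequential regression on earlier ones within arm, which approximates the mixed model when women do not return after stopping. In the last three rows, control women who had lost less by their last visit were more likely to stop; average completers were 52.7, 46.3 and 40.3 of 60.

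| Drop-out (nominal) | Completers only, kg (SE) | Using 15-day weights, kg (SE) | SE reduction |
|---|---|---|---|
| 10%, unrelated to weight | −1.00 (0.674) | −1.00 (0.658) | 2% |
| 20%, unrelated | −0.99 (0.713) | −1.00 (0.682) | 4% |
| 30%, unrelated | −0.98 (0.779) | −0.99 (0.714) | 8% |
| 10%, weight-related in control arm | −0.73 (0.681) | −0.98 (0.665) | 2% |
| 20%, weight-related in control arm | −0.55 (0.709) | −1.00 (0.690) | 3% |
| 30%, weight-related in control arm | −0.38 (0.771) | −1.00 (0.727) | 6% |

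SE reduction is 1 − (SE using interim weights ÷ SE completers only); for example 1 − 0.682/0.713 = 4%.

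**Step 4. Does the direction hold under other assumptions?** No. Drop-out was next made to depend on weight lost by day 30, with more stopping in the whey arm.
- At 12% control and 21% whey, completers-only gives −1.14 kg (SE 0.71) and the interim weights −1.00 kg (SE 0.69), an SE reduction of 1 − 0.69/0.71 = 3%.
- At 20% and 31%, the results are −1.18 kg (SE 0.75) and −1.00 kg (SE 0.69), a reduction of 8%.

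With baseline-adjusted ANCOVA in completers as the comparator, and drop-out again dependent on day-30 loss, completers gave −0.92 to −1.10 kg and the interim weights −0.99 to −1.01 kg. With 20% drop-out unrelated to weight, neither was biased and the SE fell from 0.76 to 0.69 (9%).

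**The case against.** The strongest reply is that the article never says interim weights are ignored. That is inferred from a one-paragraph Analysis section, and an unseen analysis plan could add a mixed model or imputation. Baseline-adjusted ANCOVA of the end value is a sound estimate of a 2-month effect, and without drop-out it loses next to nothing. This stands as a caution. It does not dispose of the point, because the article does state its methods, gives the E/B formula for every variable, and excludes women who stop. Followed as written, the result is a completers-only comparison.

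Three further objections stand and limit the point:
- A mixed model alone would not help, because the exclusion rules under Participants would still remove the women concerned.
- Weight and BMI are not named in the aim, which lists body composition, and the sample size rests on anandamide. The endocannabinoid and other blood outcomes have no interim values and gain nothing.
- The simulated drop-out depended on recorded weights, which is the condition under which the interim weights work. Removal of the bias is therefore built in.

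A reader might infer that the planned weight result will be biased by a known amount, or in a known direction. The documents do not support that. They give no drop-out rate or pattern, and the simulated bias changes sign with the assumption made.

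**Conclusion.** The point holds in a limited form. As written, the plan leaves recorded 15-day weights unused and removes early stoppers from the weight and BMI comparison. It is a worthwhile improvement to two outcomes rather than an error that undermines the trial.

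The gain is nil without drop-out. Under assumed drop-out of roughly 10–30%, the standard error falls by about 2–9%. Bias may be towards or away from zero, and is removed only if stopping depends on weights already recorded; stopping driven by unrecorded weight change would remain a problem. These figures rest on assumed SDs, correlations, drop-out and treatment effect, and on an approximation to the mixed model.

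**What to change.** In Analysis, for weight and for BMI, specify one mixed model for repeated measures on all 15-day values, with arm, visit, arm-by-visit interaction, baseline value, the age and BMI stratification factors, and unstructured covariance. Report the arm difference at 2 months with a 95% confidence interval as the result.

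Include all randomised women with any post-baseline weight. State explicitly that weights already recorded for women who would be excluded under Participants (unwilling to continue, pregnancy, leftover powder) stay in this analysis; without that sentence the model brings little.

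Keep baseline-adjusted ANCOVA for outcomes measured only at baseline and end.

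The cost is plan wording and a few lines of code, with no new visits or measurements. The downside is a more complex model than a t-test or ANCOVA: four post-baseline visits give 4 × 5/2 = 10 covariance parameters, estimated from at most 60 × 4 = 240 weights.
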